### *Post-TCSCS Questionnaires*

#### *Low Urinary tract assessment*

- Neurogenic Bladder Symptom Score (NBSS)
- The Incontinence-QoL (I-QoL)

#### *Bowel assessment*

- Neurogenic bowel dysfunction score (NBD Score)
- The modified Wexner fecal incontinence score (WIS)
- Time Needed for Bowel Movement (TNFBM), completed at home

#### *Sexual health assessments*

- The International Index of Erectile Function (IIEF-15) (male participants)
- The Female Sexual Function Index (FSFI) (female participants)

#### *Cardiovascular assessments*

- Autonomic dysfunctions in SCI (ADFSCI) questionnaire: Comprises of 21 questions, covering three domains, including general, medications, and autonomic dysreflexia symptoms and severity

## Visit 21-22 or 39 - 40 / Follow-Up Visits at 6 and 12 weeks after completion of stimulation protocol/Week 19 and Week 25

These visits will take place over the telephone to evaluate existing and new adverse events and concurrent treatments. During each of these follow-up phone Visits (39 and 40) at 6 and 12 weeks post completion of long term TCSCS, a series of questionnaires on low urinary tract function, bowel function, cardiovascular function and sexual health will be conducted by telephone or video conference call (considering the present COVID-19 pandemic environment). The questionnaires are listed below and details can be found in the Description of Assessments Section.

During visit 40, a sexual health clinician, with experience providing clinical care to individuals with SCI, will also conduct a semi-structured qualitative interview. Please see Description of Assessments for details.

Visit 21/39 will take approximately 1 hour and visit 22/40 will take approximately 1.5 hours.

#### *Low Urinary tract assessment*

- Neurogenic Bladder Symptom Score (NBSS)
- The Incontinence-QoL (I-QoL)

#### *Bowel assessment*

- Neurogenic bowel dysfunction score (NBD Score)
- The modified Wexner fecal incontinence score (WIS)
- Time Needed for Bowel Movement (TNFBM), completed at home

#### *Sexual health assessments*

- The International Index of Erectile Function (IIEF-15) (male participants)
- The Female Sexual Function Index (FSFI) (female participants)

#### *Cardiovascular assessments*

- Autonomic dysfunctions in SCI (ADFSCI) questionnaire

### *Descriptions of Assessments*

#### *Physical examinations*

#### *SCI severity assessment:*

- *International Standards for Neurological Classification of Spinal Cord Injury (ISNCSCI) examination:*

Neurological evaluations of participants with SCI will be performed using the ISNCSCI exam. The level and severity of damage to motor and sensory pathways will be determined by a trained physician using the standard ISNCSCI examination (2019 revision). In brief, this examination includes the assessment of motor function of key muscles in the upper and lower extremities using an established scale (muscle power graded as 0-5; for a total of 20 muscles in the four limbs) and sensory evaluation to light touch and pin prick in 28 dermatomes of the body. Sensory scores for each dermatome are assigned as 0=absent, 1=abnormal, and 2=normal. With this coding system, participants who perceive a pinprick as minimally sharp touch are assigned the same score as those who perceive it as almost normal. Perception of light touch stimuli is graded similarly. An examination of anal tone and sensation will be also conducted. The PI, [name] and his Co-Investigators, have the necessary clinical training to perform this evaluation, and will be responsible for this part of the study. This evaluation will be performed by either [name] (MD, PhD) or [name] (MD, PhD), who are both Physical Medicine and Rehabilitation physicians.

### *Procedures*

#### *TCSCS*

TCSCS will be delivered using a non-invasive central nervous system stimulator (TESCoN, SpineX Inc., CA, USA). A self adhesive round electrode placed on the skin between spinous processes at the midline over the vertebral column will function as a cathode, and two rectangular self-adhesive electrodes located

symmetrically on the skin over the iliac crests as anodes. To activate the spinal circuits known to be involved in LUT and bowel control (AIM 1), TCSCS will be delivered individually between spinous processes T10-11, T11-12, T12-L1, and L1-L2 (conus medullaris). Stimulation will be applied at various frequencies ranging between 1Hz and 90Hz. Current amplitude will start at 10mA and will be increased in incremental steps until tolerable or until responses plateau. Specific areas for electrode placement will be examined and prepared to reduce skin impedance. A temperature probe will be positioned adjacent to the cathode in order to monitor changes in skin temperature to prevent potential skin damage. TCSCS will be delivered under the supervision of either [name] or [name], who are both Physical Medicine and Rehabilitation physicians.

### Surface EMG

EMG signals will be recorded using a commercially available Delsys system and custom LabVIEW software (LabVIEW, National Instruments, USA). EMG data will be analyzed offline using custom MATLAB routines (MathWorks, Natick, USA). EMG signals will be sampled at 10KHz, bandpass filtered (5Hz-5KHz) and rectified for analysis. Potential motor targets and muscles we will record from include: T10-12= lower abdominal [rectus abdominis], L1-2= hip flexor [rectus femoris], L3= knee extensors [vastus medialis and lateralis], L4= ankle dorsiflexors (tibialis anterior), L5= long toe extensor [hallucis longus], S1= ankle plantar flexors [gastrocnemius], S2-3= knee flexion (hamstring), S2-S4 perineum (only control participants). Parameters of interest will be rectified surface EMG, time-locked to the electrical stimulation in 300 us bins. Motor evoked potential latency and amplitude will be recorded if present. Surface EMG will be recorded under the supervision of either [name] or [name], who are both Physical Medicine and Rehabilitation physicians.

### Concentric Needle EMG

Monopolar concentric needle EMG will be used to evaluate for evidence of denervation and for more sensitive evaluation of voluntary motor activity. Concentric needle EMG will only be used to examine the external anal sphincter muscle, due to the very small size of muscle.

A standard clinical monopolar needle electrode will be inserted into the external anal sphincter muscle, with additional reference surface electrodes positioned adjacent to the site of needle insertion. A ground electrode will be positioned over a nearby bony prominence (Anterior Superior Iliac Crest). EMG signals will be recorded using a commercially available pre-amplifier (1902, Cambridge Electronic Design, Cambridge UK), analog-to-digital converter (1401, Cambridge Electronic Design, Cambridge UK) and recorded in commercially available data acquisition software (Spike2, Cambridge Electronic Design, Cambridge UK). EMG signals will be sampled at 20KHz, bandpass filtered (10Hz-10KHz) and analysed offline. Concentric needle EMG will be performed by [name], who is a Physical Medicine and Rehabilitation physician.

### Urodynamics

Participants will undergo standard clinical procedures for UDS, including cystometry with water at 21°C and a filling rate of < 30 mL per minute through a 6F double lumen catheter with the participants in the supine position. Abdominal pressure will be measured with a 10F intrarectal balloon catheter. Pelvic floor electromyography will be recorded during cystometry with a surface electrode placed on the

perineum. Filling will be stopped when the participants report a sensation of fullness, at the moment of urine leakage, if blood pressure reaches levels of 180/110 mmHg, or per the request of the patient.

Following the standard clinical assessment UDS we will perform UDS with TCSCS. To assess the efficacy of short-term TCSCS' on LUT function, we will first prefill the bladder (i.e. 50-75% of cystometric capacity from the first UDS) without eliciting detrusor overactivity or autonomic dysreflexia. Then, TCSCS (as described above) will be delivered for 60 s each interspersed with 30 s rest (i.e. no stim) to optimize the configuration for each individual. Stimulation frequency and location will be guided by the results of the Baseline EMG Mapping of Spinal Cord Segments performed during visit 3.

TCSCS will be stopped when the participants report a sensation of fullness, at the moment of urine leakage, if blood pressure reaches levels of 180/110 mmHg, or per the request of the patient.

Urodynamics will be performed by a trained clinician (MD or RN) under the supervision of [name] (MD), who is a urologist.

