## Objectives, Hypotheses and Outcomes

**Objective 1:** To establish specific spatiotemporal activation maps for TCSCS at various spinal cord segments known to be involved in LUT and bowel control.

**Hypothesis 1:** In light of recent findings on the efficacy of spinal cord stimulation to improve bowel and LUT function, the optimal setting for motor responses (i.e. mapping) will be revealed during TCSCS.

**Primary outcome 1:** An individualized TCSCS map (i.e. location and stimulation parameters) to elicit optimal skeletal muscle activation corresponding to spinal cord segments involved in LUT and bowel control

**Objective 2:** To test whether targeted short-term TCSCS is safe with respect to cardiovascular consequences (e.g. autonomic dysreflexia) and can repeatedly improve LUT and bowel functions in humans with chronic SCI.

**Objective 2A) LUT function (safety/efficacy):** To test whether targeted short-term TCSCS is safe and can induce detrusor contractions (*voiding function*) while relaxing the EUS, i.e. to avoid DSD and independently enhance EUS tone (*storage function*).

**Hypothesis 2A):** In light of recent findings demonstrating TCSCS improves LUT function, we hypothesize that short-term TCSCS will improve voiding and storage functions without ACVEs.

**Outcome 2A):** Changes from baseline in the following UDS parameters for bladder capacity/compliance:

- i. Volume at the first sensation
- ii. Intravesical pressure (Pves) at the first sensation
- iii. Volume at the leakage point
- iv. Pressure at the leakage point
- v. Maximum bladder volume
- vi. Pves at the maximum bladder volume

**Objective 2B) LUT function (repeatability of TCSCS to improve UDS parameters):** To test whether targeted short-term TCSCS will repeatedly improve UDS parameters across different stimulation sessions.

**Hypothesis 2B):** TCSCS will elicit reproducible improvements in UDS parameters without ACVEs.

**Outcome 2B):** Reproducibility of changes within urodynamic parameters during stimulation will be assessed during two consecutive urodynamic procedures. UDS parameters for bladder capacity/compliance:

- i. Volume at the first sensation
- ii. Pves at the first sensation

**Objective 2C) Bowel function (safety/efficacy):** To test whether targeted short-term TCSCS is safe and can result in an immediate increase in anorectal pressure.

**Hypothesis 2C):** TCSCS will increase anorectal pressure without adverse cardiovascular effects.

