### Statistical Plan

Statistical analysis on LUT, bowel and sexual function will be performed (n = 40 with SCI).

A sample size calculation was performed using G\*power, version 3.0.10, with power set at 0.8 and  $\alpha$  at 0.05. Data from participants that match our inclusion criteria (n = 5, level of lesion C5 – T10, motor-complete AIS, A or B) were used from a recent TCSCS study. A minimum sample of 26 participants is required to detect a significant change in voiding efficiency [voided volume / (voided volume + post-void residual volume)] with short-term TCSCS (stim-off =  $37.8 \pm 40.6\%$  vs. stim-on =  $58.2 \pm 39.4\%$ , effect size = 0.510). Presently, there are no long-term TCSCS data with LUT and bowel outcomes, consistent with those proposed in this protocol, to facilitate a meaningful power calculation. Therefore, given this is a pilot trial study, and in order to account for drop out with long-term TCSCS, we aim to investigate 40 individuals with SCI (n = 40, C5 – T6). Short-term TCSCS effects on UDS parameters (AIM 2A) as well as ARM testing (AIM 2C) with or without different stimulation configurations will be assessed using a repeated measures non-parametric analysis of variance (ANOVA), i.e. Kruskal–Wallis test. Data from the repeatability portion of the study (AIM 2A) will be assessed within (same session) and between (different sessions) visits (2 and 3) using a repeated measures non-parametric ANOVA. TNFBM will also be assessed using a repeated measures non-parametric ANOVA.

Long-term TCSCS: Differences in continuous variables for questionnaire data (NBSS, NBD Score, I-QoL, IIEF-15 or FSFI) in AIM 3 will be assessed using a two-way repeated measures [baseline, immediately post long term TCSCS as well as post-interventional follow up at 6 and 12 weeks] ANOVA comparing changes between moderate and intensive TCSCS. Furthermore, UDS testing as well as 'faecal continence severity' (baseline and end of TCSCS 6-week period) will be assessed using Wilcoxon signed-rank tests within

groups. A P-value less than 0.05 will be considered statistically significant. A complete thematic analysis will be performed to collect contextual qualitative data from the sexual health interview.

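### The only power calculation is for voiding efficiency, which is not a listed outcome and whose component volumes the stimulated urodynamic run is not described as recording

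*Protocol*

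**What the plan says.** **Sample size (Statistical Plan).** "A minimum sample of 26 participants is required to detect a significant change in voiding efficiency". Efficiency is defined there as the voided share of total bladder content. The inputs come from five participants of an earlier stimulation study: 37.8% (SD 40.6) without stimulation, 58.2% (SD 39.4) with it, effect size 0.510. The test and its sidedness are not stated. The section says that no meaningful calculation is possible for the long-term outcomes. The target of 40 has a separate justification: "given this is a pilot trial study, and in order to account for drop out with long-term TCSCS".

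**Outcomes (Objectives, Hypotheses and Outcomes).** Hypothesis 2A reads "we hypothesize that short-term TCSCS will improve voiding and storage functions without ACVEs". Outcome 2A is introduced as "Changes from baseline in the following UDS parameters for bladder capacity/compliance" and lists volume and pressure at first sensation, at leakage and at maximum bladder volume. Outcome 2B repeats the two first-sensation items.

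**Procedure (Urodynamics).** The unstimulated test is a filling cystometry. For the stimulated run the bladder is prefilled to 50-75% of cystometric capacity and stimulation is "delivered for 60 s each interspersed with 30 s rest". The section then states: "TCSCS will be stopped when the participants report a sensation of fullness, at the moment of urine leakage". A blood pressure of 180/110 mmHg and the participant's request are the other two stops. Neither voided nor residual volume is mentioned.

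**The concern.** Three parts of the same document should agree and do not: the measure on which the minimum of 26 is based, the list of outcomes, and the account of what is recorded. As a measure, voiding efficiency appears only in the sample-size paragraph.

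Two things follow. First, a reader who sees 80% power and a minimum of 26 will take the short-term urodynamic aim to be adequately sized, although no power is given for any outcome it lists. Second, Hypothesis 2A promises better voiding, but no listed outcome measures emptying. A later analysis plan can choose the test for a listed outcome. It cannot analyse a residual volume that was never collected.

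**Working it through.** **Step 1: reproduce the effect size.** Inputs are from the Statistical Plan.

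- Mean change: 58.2 − 37.8 = 20.4 points.
- SD of the within-person change: √(s₁² + s₂² − 2·r·s₁·s₂). The protocol gives no correlation r. With r = 0.5: √(40.6² + 39.4² − 40.6 × 39.4) = √1601.08 = 40.01.
- Standardised change: d = 20.4 / 40.01 = 0.510, as stated.

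**Step 2: reproduce the 26.** Paired t-test with n − 1 degrees of freedom, non-centrality d·√n, alpha 0.05. At n = 26 the non-centrality is 0.510 × √26 = 2.60.

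| Test | Power at 25 | Power at 26 | Minimum n for 80% |
|---|---|---|---|
| One-sided | 0.797 | 0.812 | 26 |
| Two-sided | 0.687 | 0.705 | 33 |

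The 26 is arithmetically correct for a one-sided paired test and not for a two-sided one. One-sidedness is therefore an inference. With 40 completers, two-sided power for this effect is 0.882. The protocol plans non-parametric tests; applying the usual signed-rank efficiency of 0.955 moves the minima only to 27 and 34.

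**Step 3: compare the powered measure with the listed outcomes and the procedure.** Voiding efficiency is V / (V + R), with V the volume voided and R the residual, so both are needed with and without stimulation.

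| Item needed | Among Outcome 2A parameters? | Recording described under Urodynamics? |
|---|---|---|
| Voided volume V | No | No |
| Residual volume R | No | No |
| Voiding efficiency | No | No |

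Volume at leakage is the bladder volume when leakage begins. It is neither V nor R.

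**Step 4: what can be said for the listed outcomes.** The protocol gives no mean, SD or target change for any of the six, so no sample size can be derived. Only the smallest standardised within-person change detectable with 80% power at alpha 0.05 can be given (paired t-test):

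| Completers | One-sided | Two-sided |
|---|---|---|
| 26 | 0.50 SD | 0.57 SD |
| 40 | 0.40 SD | 0.45 SD |

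**The case against.** The strongest reply is that the Urodynamics section is not a full account. It invokes standard clinical procedure and names cystometry as something included, which leaves room for an undescribed voiding phase. The rule switches off stimulation; it does not say that recording or emptying stops, and a catheter is in place through which residual urine could be drained. The short trains serve to tune the configuration, so there may be more to the stimulated test than is written. All of this stands. A reader might infer that voiding efficiency cannot be measured, or that no voiding is measured; the text supports only that no such recording is described. Even if the volumes were taken, no listed outcome would use them.

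A reader might also infer that the stop rule is the mistake. It is not. It suits the two leakage-point outcomes and protects participants in whom, as the protocol's risk section says, urodynamics commonly provokes autonomic dysreflexia.

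Nor is the voiding hypothesis left without any data. Objective 2A describes voiding as induced detrusor contraction "while relaxing the EUS, i.e. to avoid DSD and independently enhance EUS tone", and the pressure channels and pelvic-floor electromyography can record that response. What is missing is an outcome for emptying.

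Finally, a reader might infer that 40 is unjustified. The protocol rests 40 on pilot and dropout grounds, and a pilot need not power every outcome. That reply stands for 40. It does not rescue the 26, which is still presented as a required minimum.

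**Conclusion.** The point holds as an inconsistency between the sample-size basis, the outcome list and the described procedure. The stated 80% power applies to no listed outcome, and the emptying part of Hypothesis 2A has no outcome. It is worth correcting because this is the protocol's sole power statement, but it does not put the target of 40 or the conduct of the stimulated run in question.

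In size: the 26 gives 81.2% power one-sided and 70.5% two-sided for voiding efficiency. For the listed outcomes, only the detectable changes can be stated, 0.57 SD with 26 completers and 0.45 SD with 40 (two-sided, 80% power). These figures assume a paired t-test as an approximation to the planned non-parametric analysis. The reproduction of 0.510 also assumes a within-person correlation of 0.5, which the protocol does not state.

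**What to change.** Choose one of two. Both keep 40 participants and every existing stop.

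**(a) Keep voiding efficiency and measure it.** Under Urodynamics, record voided or leaked volume and the catheter-drained residual after both the unstimulated and the stimulated run. Add voiding efficiency to Outcome 2A. In the Statistical Plan, state the test and its sidedness: 26 if one-sided, 33 if two-sided. Since 40 − 33 = 7, the two-sided requirement still leaves room for seven losses. Note that stimulation may be off before emptying is complete, so the effect may be smaller than the 20.4 points assumed. The cost is two volume measurements per run, with no added visit and no added stimulation.

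**(b) Give up voiding efficiency as the basis.** In the Statistical Plan, remove it as the reason for 26, state that 40 rests on pilot grounds, and give the detectable two-sided changes (0.57 SD with 26 completers, 0.45 SD with 40). In Hypothesis 2A, limit the voiding claim to the detrusor and sphincter response that Objective 2A already names. No procedure changes, but the trial then makes no claim about emptying.

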#### Cardiovascular monitoring

Cardiovascular monitoring will be utilised as a safety measure to detect and record potential ACVEs. such as autonomic dysreflexia, during UDS and ARM (with and without TCSCS). BP will be measured continuously (beat-by-beat) via finger photoplethysmography corrected to brachial pressure and heart rate, measured via one-lead electrocardiogram. An attending physician will monitor for potential development of episodes of autonomic dysreflexia, which is defined according to the International Standards to document remaining Autonomic Function after SCI as an increase in systolic blood pressure  $\geq 20$  mmHg from baseline. Autonomic dysreflexia will be resolved with the implementation of an established clinical management protocol in accordance with the Consortium of Spinal Cord Medicine Clinical practice guidelines (Clinical Practice guidelines provide recommendations for healthcare specialists based on evidence-based research conducted by the Consortium for Spinal Cord Medicine).

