#### ARM

This is a well-established methodology that provides a direct assessment of anal sphincter pressure and anorectal coordination during simulated defaecation. ARM is widely available, easy to perform and well accepted by participants. ARM will be repeated with TCSCS according to the protocol for TCSCS application as described above. Stimulation frequency, location and intensity during ARM will be guided by the results of the Baseline EMG Mapping of Spinal Cord Segments performed during visit 3 and by our ability to activate S2-S4 innervated muscles (spinal cord segments crucial for anorectal sphincter control).

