- With TCSCS we do not expect adverse events as our study will only utilize parameters and electrodes approved in previous studies. Stimulation could potentially irritate the skin, so we will monitor skin temperature for potential irritation. TCSCS elicit AD, however so far no AD/OH is observed in TCSCS studies. Furthermore, cessation in stimulation immediately reduces blood pressure, and we will be monitoring blood pressure closely during procedures. In case of adverse

events, the participant's primary physician would be notified as needed. Participants will be continuously monitored for any signs of risks or discomfort. As mentioned, we will also continuously monitor cardiovascular signals such as blood pressure and heart rate. For TCSCS, we will additionally measure skin temperature.

- In this study, participants will be asked to undergo UDS, a clinically approved procedure for examination of urinary bladder function in participants with injury to the central or periphery nervous system. This procedure is typically recommended to be performed on a biannual basis in participants with multiple sclerosis, stroke, and SCI, in order to establish urine bladder function. It is known that within the SCI population, UDS commonly elicits episodes of AD in participants with injury at the T6 spinal segment and above (an inclusion criteria for the present study). Clinically, UDS is an important component of bladder function evaluation following SCI. Risk management in this study involves having trained personnel performing these studies in a clinical facility with protocols in place to manage iatrogenic/artificially induced episodes of AD. All these criteria are in place at the site of the Principal Investigator, located at the ICORD/Blusson Spinal Cord Injury Centre at the Vancouver General Hospital.
- Concentric needle EMG is a common clinical procedure, performed in a variety of clinical settings worldwide. The risks of EMG are very small and include small risk of bleeding, bruising and mild discomfort that can last up to 24 hours. EMG is very well tolerated and the risks will be minimized by localizing the target muscles using well-established surface anatomical landmarks in order to avoid placement in proximity to blood vessels or nerves. In the event of discomfort during the procedure, this will be minimized simply by moving the needle to a slightly different position.

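### Current escalation at the Visit 3 mapping session has no blood-pressure stop, and the specified cardiovascular monitoring is not assigned to that visit

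*Protocol*

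**What the plan says.** All references are to the protocol.

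- **TCSCS** (under Procedures): stimulation is given at four interspinous sites from T10-11 to L1-L2, at 1 to 90 Hz. Current begins at 10 mA and "will be increased in incremental steps until tolerable or until responses plateau". The safety signal named here is skin temperature. Delivery is supervised by a physician.
- **Visit 3** (baseline EMG mapping): refers the reader to the TCSCS, Surface EMG and Concentric Needle EMG subsections. It does not refer to Cardiovascular monitoring.
- **Cardiovascular monitoring**: beat-by-beat pressure, one-lead ECG and an attending physician are used to detect "potential ACVEs. such as autonomic dysreflexia, during UDS and ARM (with and without TCSCS"). Dysreflexia is defined as a systolic rise of at least 20 mmHg from baseline. The section for Visits 4, 5 and 6 gives the same scope.
- **Urodynamics**: "TCSCS will be stopped when the participants report a sensation of fullness, at the moment of urine leakage", and also "if blood pressure reaches levels of 180/110 mmHg, or per the request of the patient". The same pressure limit applies to bladder filling.
- **ARM**: "ARM will be repeated with TCSCS according to the protocol for TCSCS application as described above". No pressure limit of its own.
- **Long Term TCSCS Visits**: pressure and heart rate once a minute. No stop value.
- **Known Study Risks/Harms**: a session stops if an adverse event occurs, with no pressure value given. The bullet on stimulation says that "cessation in stimulation immediately reduces blood pressure, and we will be monitoring blood pressure closely during procedures", that "we will also continuously monitor cardiovascular signals such as blood pressure and heart rate", and then "For TCSCS, we will additionally measure skin temperature".
- **Managing episodes of AD**: drug treatment starts if pressure remains above 150 mmHg after the non-drug steps.

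**The concern.** All participants are injured at or above T6 with AIS A or B, the group in which the protocol expects dysreflexia during urodynamics. The background section says that stimulation below the injury should be checked for cardiovascular safety. Visit 3 is the first exposure, and there current is raised step by step across several sites and frequencies before the individual response is known.

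As written, the rule for raising current ends on tolerance or a plateau in the response. In motor-complete injury with electrodes at T10 to L2, reported tolerance may be a weak guide to a pressure rise. That is my clinical inference; the protocol does not discuss it. A member of staff who saw pressure climbing during mapping would find no number in the TCSCS section at which to stop. The sponsor evidently regards a pressure limit as appropriate for stimulation, having written one for urodynamics. Since the protocol says pressure falls at once when stimulation ceases, a written limit could be acted on immediately.

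Stimulation stop rules and procedural monitoring belong in the protocol, so this is not a matter left to an analysis plan.

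**Working it through.** No figure in the protocol is at issue, so the check sets the four stimulation settings side by side.

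| Setting | Visits per participant | Pressure monitoring stated | Pressure value that stops stimulation |
|---|---|---|---|
| Mapping (Visit 3) | 1 | Promised in the risk section; no method assigned | None |
| Urodynamics (two of Visits 4-6) | 2 | Beat-by-beat, ECG, physician | 180/110 mmHg |
| ARM (one of Visits 4-6) | 1 | Beat-by-beat, ECG, physician | None of its own; possibly inherited from Urodynamics |
| Long-term sessions | 12 or 30 | Once a minute | None |

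**Endpoints.** The TCSCS section gives two endpoints for raising current (tolerance, plateau), and neither is a pressure. The Urodynamics section gives four conditions for stopping stimulation (fullness, leakage, pressure, request), and one is a pressure.

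**Where open-ended escalation applies.** The TCSCS section links stimulation of each site in turn to Aim 1, which is mapping. The ARM section says its intensity is guided by the mapping results. The long-term section repeats the electrode and skin-temperature set-up but not the escalation sentence. Escalation without a pressure endpoint is therefore clearly assigned to mapping only: 40 × 1 = 40 visits at full enrolment.

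**Where a stop value is absent.** Visits with stimulation, counting Visits 3 to 6 and the treatment sessions:
- Moderate group: 1 + 2 + 1 + 12 = 16. Clearly without a value: 1 + 12 = 13, or 14 if ARM is counted.
- Intense group: 1 + 2 + 1 + 30 = 34. Clearly without a value: 1 + 30 = 31, or 32 if ARM is counted.

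Of these, only the single mapping visit combines escalating current with no assigned monitoring method.

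**Which value to use.** The protocol gives no resting pressure. Assume a resting systolic of 90 to 120 mmHg:
- The dysreflexia definition is met at 90 + 20 = 110 to 120 + 20 = 140 mmHg.
- The urodynamics ceiling lies 180 − 140 = 40 to 180 − 110 = 70 mmHg higher.
- The ceiling also lies 180 − 150 = 30 mmHg above the level for drug treatment, reading that level as systolic.

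Copying 180/110 mmHg alone into the TCSCS section could thus be read as allowing stimulation to continue through dysreflexia. A lower trigger has to accompany it.

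**The case against.** The strongest reply is that a stop can already be derived. Dysreflexia is named as an adverse cardiovascular event and defined at 20 mmHg, sessions stop on an adverse event, and the risk section promises the monitoring that would detect it. On that reading, the higher urodynamics limit is a local exception, because bladder filling itself often provokes dysreflexia. This has force, and it rules out saying that stimulation outside urodynamics has no stop of any kind. It does not settle the point. The adverse-event rule carries no pressure value, and the only number the protocol attaches to stopping stimulation is 180/110 mmHg. The reader must infer which applies while current is being raised.

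Several other replies stand:
- The ARM section's reference to what is described above may carry over the urodynamics stop, since that section precedes it. ARM is arguably covered.
- Long-term sessions do measure pressure every minute.
- How a resting reading is taken, and monitoring during needle EMG, are operational details and not faults in themselves.
- The Visit 3 section cites an established protocol, and the overview cites a schedule of events. Neither is shown, and either might fill the gap.
- The protocol reports no dysreflexia so far in studies of this stimulation.

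A reader might infer that pressure goes unmonitored at mapping, or that current is raised without a limit at 14 or 32 visits per participant. The text supports neither. Monitoring is promised and physicians supervise, and escalation is clearly assigned to one visit.

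**Conclusion.** The point holds in a limited form and should be fixed. Followed literally, the escalation rule and the stated scope of cardiovascular monitoring leave out, at first exposure, a safeguard that the sponsor applies to the same stimulation during urodynamics. It concerns one mapping visit for each of 40 participants. The absence of a stop value in the 12 or 30 long-term sessions is a lesser gap, because pressure is already read every minute there.

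The monitoring and risk sections do not flatly contradict each other: the former does not say that its method is used only in urodynamics and ARM. The fault is a promise whose method is not assigned to the visit that most needs it.

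The conclusion rests on the text shown. It would weaken if the established mapping protocol or the schedule of events contains a pressure limit and a monitoring method. The 40 to 70 mmHg distance depends on the assumed resting systolic of 90 to 120 mmHg. No sample-size or efficacy analysis is affected.

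**What to change.** 1. **Cardiovascular monitoring:** extend the scope to mapping (Visit 3), urodynamics and ARM, and cite this section in the Visit 3 text.
2. **TCSCS and Long Term TCSCS Visits:** state that current is raised no further and stimulation stops when dysreflexia as already defined occurs, meaning a systolic rise of at least 20 mmHg from a resting reading taken before stimulation. Add that it stops in any case no later than 180/110 mmHg. With both parts, the ceiling does not override the adverse-event stop or the 150 mmHg treatment step.
3. **Urodynamics:** because this section refers back to the TCSCS section, add a clause saying whether its own stop rule is unchanged. I would leave it, since filling alone can raise pressure there.

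The cost is protocol wording, a slightly longer set-up at Visit 3 for the pressure and ECG recording, and some mapping runs ended before a plateau. ARM and long-term sessions already measure pressure, so they need no new equipment or readings beyond the resting one.
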